#### 2. Learning curve analysis.

A learning curve analysis will be conducted to assess whether the procedural efficacy and efficiency improve with operator experience using the novel system. The first 50 consecutively enrolled patients in the intervention arm (irrespective of the performing operator) will be defined as the ‘early experience’ cohort, and will be compared with all subsequent intervention arm patients (‘established experience’ cohort) on the primary endpoint (forearm RAO incidence) and key procedural efficiency metrics (total hemostasis time). The 50-case cutoff was set based on pre-trial pilot data indicating that operators achieve stable proficiency after approximately 50 procedures [19].

We acknowledge that this cohort-based (rather than operator-based) approach may blend cases from operators at different points in their individual learning curves. Therefore, to evaluate the robustness of the findings, a sensitivity analysis will be conducted by repeating the comparison using only data from the two highest-enrolling operators, with the aim of reducing heterogeneity and provide a more direct assessment of the learning effect within individual operators.

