### Operator training and quality control (integrated for bias mitigation)

Given the unblinded nature of operators, rigorous training and quality control will be implemented to reduce performance and detection bias, as these measures are critical for minimizing bias from non-blinded personnel:

Operator qualifications: all staff directly performing balloon pressure monitoring or assessing hemostatic efficacy will be selected from the study team and possess the required clinical credentials and routine work experience, including interventional procedures and post-procedural care.Standardized training: before trial initiation, all relevant personnel must complete a half-day centralized training. This training will cover detailed interpretation of the study protocol and procedures; principles of the system, device calibration, and demonstration of standardized operational workflows; identification and management protocols for endpoint events (e.g., forearm RAO, bleeding, hematoma); and standardized completion of case report forms (CRFs) and data management requirements.Qualification assessment: after training, each operator must successfully complete the full operational workflow for at least three simulated or real patients under the supervision of the PI or a designated supervisor. Formal qualification is granted only after confirming that the operator can execute the protocol accurately and consistently.Ongoing quality monitoring, which will be implemented as follows:(a) Periodic review: the PI will regularly audit procedural records and data to ensure protocol adherence.(b) Adverse event review: any procedure-related adverse events will trigger team discussions and retraining if necessary.(c) Blinded assessment: the primary endpoint (24-hour RAO) will be assessed by a blinded ultrasonographer to eliminate measurement bias.(d) Protocol compliance review: an independent team led by the PI will conduct periodic blinded reviews of procedural records, with group allocation concealed, to identify and address deviations.(e) Quality control for data collection of key processes: To ensure the consistency and accuracy of the high-frequency recording for key process metrics such as “active operator time,” the following measures will be implemented: (i) a designated, trained research nurse will be held solely responsible for timestamp documentation across all cases; (ii) Validated, standardized, and user-friendly timing tools (e.g., dedicated timers or tablet applications) will be used to assist in recording the timestamps of the key operational nodes. The following predefined strategy for handling missing data has already been established in the statistical plan: if the data missing rate is < 10%, a complete-case analysis will be adopted; if the missing rate is ≥ 10%, multiple imputation will be applied in sensitivity analyzes to systematically assess the potential impact of data missingness on the primary study conclusions. (iii) Specialized training for research nurses: Nurses will receive targeted training regarding the definition of “direct hands-on tasks” (including pressure adjustment, bleeding assessment, device calibration, and data documentation related to hemostasis; excluding passive observation, waiting, or auxiliary tasks not directly involved in hemostasis). Training will include the case simulations of complex scenarios (e.g., simultaneous multi-operator activities) to ensure consistent identification of task start/end times.

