### Intervention: Operating procedure of the system

The standardized operational procedure for the balloon pressure monitoring system is summarized in Fig 4 (left panel) and detailed as follows:

Initial compression: Immediately following sheath removal, the balloon is inflated to a target pressure of 260 mmHg. (This pressure, derived from a pre-trial pilot study (n = 32), ensures reliable immediate hemostasis with no associated neurovascular or skin injuries.)Individualized minimum effective hemostatic pressure titration: The balloon pressure is gradually decreased until slight oozing is observed at the puncture site. Then, the pressure is incrementally increased in steps of 20 mmHg until bleeding ceases. This value is recorded as the patient’s initial hemostatic threshold.Phased decompression and monitoring: At 30 minutes post-procedure, the pressure is adjusted to 60 mmHg (an intermediate value based on the hemostatic threshold, with fine-tuning for bleeding status). At 60, 90, and 120 minutes post-procedure, pressure is reduced by 30 mmHg at each interval until it reaches zero.Bleeding management: If bleeding occurs at any stage, pressure is increased in 20 mmHg steps until hemostasis is reestablished.Documentation: All pressure values, operation times, and involved personnel are recorded throughout the procedure to ensure traceability.

(The parameters for this procedure—including the initial pressure, titration step, and decompression schedule—were derived from a preceding pilot study.)

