### Distinctive design features of the present trial

This trial incorporates several key design strengths to ensure robust and clinically relevant evidence:

Superiority Design with Clinically Meaningful Endpoint: This trial is powered to detect a pre-specified 3.3% absolute risk reduction in 24-hour RAO (clinically significant, benchmarked against real-world and best-practice targets).Standardization and Bias Mitigation: While operator blinding is not feasible, rigorous measures will be implemented to minimize bias, including standardized training, a unified control protocol, and blinded assessment of the primary endpoint by independent ultrasonographers.Operator Proficiency and Real-World Validity: Operators will be required to complete the structured training and demonstrate competency, thus ensuring the intervention is tested under conditions of proficient use. The broad inclusion/exclusion criteria ensure a population representative of routine clinical practice.Comprehensive Endpoint Assessment: Beyond the primary efficacy endpoint, the trial systematically evaluates key secondary outcomes, including vascular complications, bleeding events, and (uniquely) objective metrics of procedural burden (e.g., active operator time), providing a holistic view of the system’s clinical utility.

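### The learning-curve cutoff of 50 is justified as a per-operator figure but applied to the first 50 intervention patients pooled over operators, and its source is not reconciled with the only pilot of stated size

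*Protocol article*

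**What the plan says.** The subsection on learning curve analysis divides the intervention arm in two. "The first 50 consecutively enrolled patients in the intervention arm (irrespective of the performing operator) will be defined as the" early-experience cohort, and all later intervention patients form the established-experience cohort. The two are compared on 24-hour forearm radial artery occlusion (RAO) and on total hemostasis time.

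The reason given for the number is "The 50-case cutoff was set based on pre-trial pilot data indicating that operators achieve stable proficiency after approximately 50 procedures", followed by a citation to reference 19.

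The same subsection concedes that "this cohort-based (rather than operator-based) approach may blend cases from operators at different points in their individual learning curves". In response it plans a sensitivity analysis, "repeating the comparison using only data from the two highest-enrolling operators", intended to give a more direct view of learning within individual operators.

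A pilot study appears in one other place, the operating procedure of the system. There the initial balloon pressure is "derived from a pre-trial pilot study" with n = 32, and the other procedure parameters are also attributed to a preceding pilot. No other pilot is described and no other size is given. The same section says that the personnel involved in each procedure are recorded.

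**The concern.** The justification and the rule use different units. The justification says how many procedures an operator needs before performance is stable. The rule counts patients in the arm, whoever treated them. When several operators share the work, most have done far fewer than 50 procedures when the arm reaches its 50th patient. By the plan's own figure, part of the established cohort is then still early experience, and the cohort's label does not describe it.

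The source of the figure raises a second question. A pilot of 32 procedures ends before the 50th, so it could not by itself have shown where performance levels off near 50.

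What is at stake is how an exploratory result can be read. The limitations section names the learning curve as a limitation and points to this analysis as the way it will be quantified. The analysis should therefore measure what its label says.

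**Working it through.** **Inputs.** From the protocol: 409 patients per group (sample size section); the cutoff of 50 and its pooled application (learning curve subsection); pilot n = 32 (operating procedure section); planned RAO of 1.0% in the intervention group (sample size section). Assumed: k operators with equal caseload, each counted from the first trial case with the system. The protocol does not give k. It does refer to the two highest-enrolling operators, so k is at least 2.

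**Arm size.** With 4.3% versus 1.0%, two-sided α of 0.05 and 80% power, the unpooled normal approximation gives 368 per arm, or 736 in total. Then 736/0.90 = 817.8, rounded up to 818, which is 409 per group. This matches the protocol. The established cohort is 409 − 50 = 359. The cutoff of 50 has no formula to reproduce.

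**Unit of the cutoff.** The first 50 arm patients give each operator 50/k cases. All of these lie within the operators' own first 50. The arm contains 50k cases that fall within some operator's first 50, as long as 50k does not exceed 409. Subtracting the 50 already labelled early leaves 50k − 50 in the established cohort, a share of (50k − 50)/359.

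| k | Cases per operator in the early cohort, 50/k | Established patients within their operator's first 50, 50k − 50 | Share of 359 |
|---|---|---|---|
| 2 | 25 | 50 | 14% |
| 3 | 16.7 | 100 | 28% |
| 4 | 12.5 | 150 | 42% |
| 6 | 8.3 | 250 | 70% |
| 8 | 6.25 | 350 | 97% |

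At k = 1 the share is zero, the only case in which the two units agree. Since 409/50 = 8.2, with nine or more equal operators nobody completes 50 cases. With unequal caseloads, an operator who does fewer than 50 cases contributes only that smaller number, so the share is lower than the table shows for the same k.

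**Sensitivity analysis.** Restricting to two operators while keeping a pooled count of 50 leaves at most 25 early cases per operator on average (50/2). The text states no count or cutoff within each operator.

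**Pilot.** 50 − 32 = 18. Even if one operator had done every pilot case, the pilot would stop 18 procedures short of the stated plateau. Shared by two operators it gives 16 cases each, and by four it gives 8.

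**RAO events.** At 1.0%, the early cohort expects 50 × 0.01 = 0.5 events, and the chance of none is 0.99^50 = 0.605, or 61%. The established cohort expects 359 × 0.01 = 3.6.

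**The case against.** The protocol does not hide the pooling. It states the limitation openly and adds a sensitivity analysis because of it, and that deserves credit. But the sensitivity analysis repeats the same comparison in fewer operators and does not index cases within an operator. The disclosure also leaves the stated basis for the number 50 as it was. An article may leave operator-level detail to the full protocol or analysis plan, but here the rule and its reason are both given and do not match.

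A reader might infer that the cutoff has no empirical basis. The documents do not support that. The n = 32 pilot is tied to the pressure and decompression parameters, not to operator proficiency, and reference 19, which cannot be checked here, or another dataset may be the source. What stands is that the text does not reconcile the two statements.

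A reader might also infer that the analysis is bound to show no learning effect, and that such a result would then be used to defend the claim in the design features section, "thus ensuring the intervention is tested under conditions of proficient use". Neither follows. The shares above measure mislabelling, not the size of a bias, and steep early learning could still show in a pooled split. Nothing in the protocol says a null result would be used in that way.

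Nor does the training section conflict with that claim merely because "each operator must successfully complete the full operational workflow for at least three simulated or real patients". Three is a minimum, and qualification also requires confirmation of accurate and consistent performance.

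Finally, the low number of RAO events does not expose a faulty test. The statistical methods already make exploratory analyses purely descriptive, and this subsection names no test.

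**Conclusion.** The point holds in a limited form. A figure worded for operators is applied to a pooled count, and the planned sensitivity analysis does not secure the within-operator assessment it aims for. With equal caseload, 14% of the established cohort would be mislabelled by the plan's own figure with two operators, rising to 97% with eight. These shares depend on an operator number the protocol does not give, on equal caseload, and on counting from each operator's first trial case. Reading 50 as a team total would remove the mismatch of units, but it is not the natural reading of the sentence, and a pilot of 32 could not by itself support that reading either.

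The source of 50 needs clarifying; it has not been shown to be wrong. The consequence is small, because the analysis is exploratory and the primary comparison, the sample size and the error rate are untouched.

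**What to change.** 1. Number each operator's intervention cases in order, using the personnel already recorded for every procedure. Define early and established experience by that number, or plot and model hemostasis time against it, at least in the sensitivity analysis.
2. Keep RAO by experience as descriptive counts.
3. Name the dataset behind the figure of 50, with its size and number of operators, and say how it relates to the n = 32 pilot. Otherwise call 50 a pragmatic cutoff.

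A mixed model with the control arm as a calendar reference is one way to do the modelling, but it is a preference and not needed to settle the point.

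The cost is a little more analysis work on data already collected, and a sentence of text. The drawback is that few established cases may remain when many operators share the arm: under equal caseload 409 − 50k, which is 209 for four operators, 9 for eight and none for nine or more. In that situation, plotting time against case number uses the data better than a split at 50.

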### Interim analysis and stopping guidelines

Given that there is only a single primary endpoint which will be assessed at 24 h, no formal interim efficacy analysis is planned. However, the independent DSMB will conduct periodic reviews of the unblinded safety data (after every 200 enrolled patients) per predefined charter, and may recommend early trial termination only for compelling safety concerns.

### Trial monitoring

Trial conduct will be monitored through a combination of independent safety oversight and internal quality audits to ensure protocol adherence, data integrity, and participant safety.

#### 1. Independent Safety Monitoring.

The independent DSMB, as described in the Interim Analysis and Stopping Guidelines section, is responsible for safety monitoring. The DSMB will convene after every 200 participants are enrolled to review unblinded safety data.

#### 2. Internal Quality Audits.

The PI and the study coordination team will conduct internal audits of protocol compliance and data quality on a quarterly basis. Audit procedures will include:

(a) Reviewing a random sample of CRFs against source documents for accuracy and completeness.(b) Verifying adherence to randomization and intervention assignment procedures.(c) Assessing the documentation of protocol deviations and informed consent.(d) Evaluating the completeness of data collection for primary and secondary endpoints.

Findings from both DSMB reviews and internal audits will be formally documented. Any significant issues identified will be reported to the Steering Committee, and corrective actions will be implemented promptly.

### Statistical software

All analyzes will be conducted using validated software (SPSS version 26.0, IBM Corp., Armonk, NY, USA; or R version 4.2.0, R Foundation for Statistical Computing, Vienna, Austria) by an independent statistician blinded to the treatment group allocation.

### Ethical approval and study oversight

This study protocol has been approved by the Medical Ethics Committee of Nanjing Lishui People’s Hospital (approval number: 2024KY0726−01) and was registered with the Chinese Clinical Trial Registry (registration number: ChiCTR2400088258). The trial will be conducted in accordance with the principles of the Declaration of Helsinki, and written informed consent will be obtained from all participants prior to enrollment.

An independent DSMB, comprising clinical experts and statisticians not involved in trial conduct, will periodically (after every 200 enrolled patients) review the unblinded safety data to assess the risk-benefit balance and provide recommendations for trial continuation, modification, or termination. The main trial results are expected to be submitted for publication in a peer-reviewed journal by the end of 2026.

## Discussion

### Positioning and innovation of this study in the evidence chain

TRA is the established default strategy for coronary procedures, given its demonstrated advantages in safety and patient outcomes over transfemoral access [1,2]. Despite this, forearm RAO remains the most common procedural complication [1,2], and a significant “efficacy-effectiveness gap” persists: while optimized research protocols [1] can achieve RAO rates below 5% under controlled conditions, the real-world incidence remains as high as 33% [3]. This gap compromises the utility of the radial artery for future interventions, and originates primarily from the limitations inherent in patent hemostasis—the cornerstone of RAO prevention [2,3].

Clinically, patent hemostasis relies on operator-dependent, intermittent assessments and empirical pressure titration, leading to poor standardization, high inter-operator variability, and failure to achieve any true patency in a substantial proportion of real-world patients [2,3]. Methodologically, the existing evidence base is fragmented, characterized by a predominance of single-center or non-randomized designs, significant heterogeneity in devices and protocols, and inconsistent definitions and assessments of RAO [2,6,7]. These limitations obscure the true treatment effects and hinder the translation of research findings into practice [8,9]. Although intensive, multi-component “best-practice bundles” have achieved remarkably low RAO rates in trials, their complexity and resource demands limit their broad implementation, thus underscoring the need for a simplified, objective, and scalable approach to patent hemostasis [2,4].

The innovation of this study lies in addressing the external validity challenge [11]: traditional hemostasis’ lack of standardization decouples trial results from clinical practice. Our system bridges this gap via two core innovations to standardize hemostasis: 1) Quantitative pressure control: Replacing empirical volume-based compression with high-precision (± 3.75 mmHg) digital manometry to directly measure vascular wall pressure in real time; 2) Physiologically phased decompression: Synchronizing compression release with vascular repair stages (thrombus stabilization, endothelial activation, inflammatory clearance) via real-time bleeding status (not rigid time intervals).

As the first large-scale randomized controlled trial focusing on a digital manometry-guided hemostasis system for RAO prevention, this study occupies a pivotal position in the evidence chain. It seeks not to replace consensus guidelines, but to enable their reliable implementation by providing the objective control and standardization that traditional methods lack. We hypothesize that this system could consistently replicate the low RAO rates achieved by complex research protocols by precisely controlling the core biomechanical variable of the vascular wall pressure, thereby bridging the gap between evidence-based recommendation and routine clinical practice with a scalable solution for radial artery preservation.

### Distinctive design features of the present trial

This trial incorporates several key design strengths to ensure robust and clinically relevant evidence:

Superiority Design with Clinically Meaningful Endpoint: This trial is powered to detect a pre-specified 3.3% absolute risk reduction in 24-hour RAO (clinically significant, benchmarked against real-world and best-practice targets).Standardization and Bias Mitigation: While operator blinding is not feasible, rigorous measures will be implemented to minimize bias, including standardized training, a unified control protocol, and blinded assessment of the primary endpoint by independent ultrasonographers.Operator Proficiency and Real-World Validity: Operators will be required to complete the structured training and demonstrate competency, thus ensuring the intervention is tested under conditions of proficient use. The broad inclusion/exclusion criteria ensure a population representative of routine clinical practice.Comprehensive Endpoint Assessment: Beyond the primary efficacy endpoint, the trial systematically evaluates key secondary outcomes, including vascular complications, bleeding events, and (uniquely) objective metrics of procedural burden (e.g., active operator time), providing a holistic view of the system’s clinical utility.

### Potential clinical implications and scientific contribution

If this trial demonstrates the superiority of the system, it should provide high-level evidence supporting a paradigm shift toward objective, biomechanically-guided post-procedural care. Clinically, it would offer interventional cardiologists a standardized, user-friendly tool to consistently achieve patent hemostasis, potentially reducing the incidence of forearm RAO closer to the benchmarks set by complex research protocols. This could further solidify the safety profile of the transradial approach and enhance the long-term sustainability for patients requiring repeated vascular access.

From a methodological perspective, this trial advocates for the standardization and objectification of a key procedural step. The success of the study would underscore the importance of precise biomechanical control in vascular injury management and could stimulate innovation in smart, closed-loop hemostasis devices, advancing the field from artisanal skill toward reproducible engineering. Ultimately, by transforming hemostasis from an operator-dependent art into a standardized, physiology-guided procedure, this system should set a new benchmark for reproducible vascular access site management.

